### Determination of the counterfactuals for comparison

Since there is no enrolled comparison group in this study, the counterfactuals to be included to determine how effective BBM is will be threefold:Versus similar New Zealand population. The estimated mean weight change of ethnic/gender/age groups will be derived from the last five years of NZ Health Surveys [15] and these will be compared with the general programme groups participating in BBM. Note that, longitudinally, weight change in a subpopulation is the additive effects of secular changes to weight (ie each age group gets a little heavier each year) and age-related weight change (ie the person moves to an older age group which has a higher average weight).Versus control groups in other similar studies. A literature review [16] has identified five weight loss studies with predominantly Pacific or Māori participants that had control groups (total *N* = 955, follow-up 3–24 months) [17–21]. Their weight change trajectories will be compared to the BBM general programme participants.Versus other interventions. The literature review noted above [16] identified 18 studies with various interventions with weight change outcomes [17–34]. These combined results show how effective other programmes have been. Since the duration of interventions varies (3–24 months), weight loss is not linear.

A mixed method meta-analysis was conducted using the metaphor package [35] in R. Studies were only included in this analysis where the difference with baseline (time 0) was published together with their standard error, standard deviation, or confidence interval (to enable calculation of the standard error). Figure 1 shows the forest plot of the included studies.

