**Fig. 3 Fig3:**
[figure not shown]
Forest plot of the standard errors from the studies used in the meta-analysis

Weight for both the general BBM and the FTC cohorts will be analysed as with a general linear mixed model for repeated measures, with person (participant) as the random variable and time as the fixed variable. The two cohorts will be combined because some general BBM members may previously have been FTC participants, and some FTC participants subsequently become general members. The weights will be logarithmic transformed before analysis, if the residual analysis indicates that. The comparison of our study data with the tick shaped curve prediction model generated from the literature (Fig. 2) will be done by comparing specific points in time and calculating the t-probability of being equal on basis of their 95% confidence intervals.

The FTC group will be considered as a series of three cohorts of about 20 participants each entering the FTC programme. An estimate of 80% recruitment into the study will give 50 participants who will have baseline and follow up data. There is also no parallel comparison group for this part of the study. However, their weight change trajectories can also be compared with the counterfactuals noted above. FTC data will be analysed with a Difference in Difference (DID) analysis using the estimated covariance matrix from the repeated measures analysis to obtain the corrected differences (Treatment – Baseline) – (Control – Baseline) as an estimate of the effect of the programme.

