### Analysis of hua oranga scores

The hua oranga scores will be analysed with a general or generalised linear mixed model with proper distribution (gaussian, binomial or poisson) depending on the characteristics of the distribution of the outcomes. The random term is the person (participant). The scores per domain will be analysed as well as the sum of all the scores. Because we have pre- and post-data, all analyses will be followed with a DID analysis to obtain the corrected differences.

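### The planned difference-in-difference analyses cannot be estimated from the stated models: Hua Oranga has no control at all, and FTC weight needs a named external control with its own variance.

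*Protocol article*

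**What the plan says.** Under Determination of the counterfactuals for comparison, the protocol article says: "Since there is no enrolled comparison group in this study, the counterfactuals to be included to determine how effective BBM is will be threefold". The three sources listed are national health survey weights, control groups from other studies, and intervention results from other studies. All three concern weight. On the second, the literature review "has identified five weight loss studies with predominantly Pacific or Māori participants that had control groups (total *N* = 955, follow-up 3–24 months").

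The text after Fig. 3 describes one weight model, "with person (participant) as the random variable and time as the fixed variable". It pools the general and FTC participants: "The two cohorts will be combined because some general BBM members may previously have been FTC participants". For FTC it then says "There is also no parallel comparison group for this part of the study" and adds "However, their weight change trajectories can also be compared with the counterfactuals noted above". The next sentence reads "FTC data will be analysed with a Difference in Difference (DID) analysis using the estimated covariance matrix from the repeated measures analysis". The contrast is written as treatment change from baseline minus control change from baseline and is described as estimating the programme's effect. Who supplies the control change is not said.

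Under Analysis of hua oranga scores, each domain and the total are to be modelled with person as the random term, and then: "Because we have pre- and post-data, all analyses will be followed with a DID analysis to obtain the corrected differences".

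**The concern.** A difference-in-difference needs two changes over time, one in a treated group and one in an untreated group. This study measures only people in the programme. The article nevertheless fixes the method, the formula, the source of the variance and, for Hua Oranga, the reason for using it. These do not fit its own statement that there is no comparison group, so this is more than detail left to an analysis plan.

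For Hua Oranga, a declared secondary outcome, a plain pre-post change could be published as a corrected difference, which readers would take to be controlled.

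For FTC weight, the estimate depends on which control is meant. The survey trend, the literature controls and the no-change counterfactual that the Discussion calls plausible can each give a different answer; under no change, the result is simply the pre-post change. If an external control is used but the variance comes from the study's own covariance matrix alone, the interval omits the uncertainty of the control.

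**Working it through.** **Step 1. The article's own figure.** Three FTC cohorts of about 20 at 80% recruitment give 3 × 20 × 0.80 = 48, which agrees with the stated 50 to within rounding. I use 50 below.

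**Step 2. Is the contrast estimable?** Write the mean for group g (1 = programme, 0 = control) at time t as μ + a_t + g·b + g·c_t, with a_0 = c_0 = 0. The difference-in-difference at time t is c_t. If every participant has g = 1, the data inform only μ + b and a_t + c_t, so c_t cannot be separated from a_t.

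A rank check confirms this. A contrast is estimable only if adding it as a row leaves the rank of the design matrix unchanged.

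| Outcome and times | Data | Rank / columns | DID estimable? |
|---|---|---|---|
| Weight at 0, 6, 12, 24 months | participants only | 4 / 8 | no |
| Weight at 0, 6, 12, 24 months | with a control group | 8 / 8 | yes |
| Hua Oranga, pre and post | participants only | 2 / 4 | no |
| Hua Oranga, pre and post | with a control group | 4 / 4 | yes |

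The time-only model as described has full rank (4 of 4 for weight, 2 of 2 for Hua Oranga). What it identifies is the change over time, a single difference.

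**Step 3. Can an outside source supply the control change?**
- Hua Oranga: no. None of the three counterfactuals is described as carrying this scale.
- FTC weight: yes. The five control-group studies (N = 955, 3–24 months) report weight change, and the article's meta-analysis models change from a zero baseline for controls as well as interventions.

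**Step 4. Variance for FTC weight.** For independent sources, SE(difference) = √[SE(FTC change)² + SE(literature-control change)²]. The study's covariance matrix supplies only the first term. The article gives neither SE, so these are assumptions: SD of weight change 5 or 8 kg, n = 50, literature SE from 0.5 to 1.7 kg.

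First term: 5/√50 = 0.71 kg; 8/√50 = 1.13 kg.

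| Literature SE (kg) | Combined SE, SD 5 (kg) | Combined SE, SD 8 (kg) |
|---|---|---|
| 0.5 | 0.87 | 1.24 |
| 1.0 | 1.22 | 1.51 |
| 1.5 | 1.66 | 1.88 |
| 1.7 | 1.84 | 2.04 |

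The SE therefore rises from 0.71–1.13 kg to 0.87–2.04 kg. With n = 48 the figures are nearly the same: 0.72–1.15 kg to 0.88–2.06 kg.

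**Step 5. Effect on error rates.** If the second term is left out, the true two-sided error at a nominal 5% is 2[1 − Φ(1.96 × SE(FTC)/SE(combined))]. Over the table this runs from about 7% (SD 8, literature SE 0.5) to about 45% (SD 5, literature SE 1.7).

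**Step 6. What drives the literature SE.** Suppose the five control studies have a between-study SD of 1.5 kg (assumed) and within-study error is ignored. The SE of their mean is 1.5/√5 = 0.67 kg. With SD 8 the combined SE is √(1.13² + 0.67²) = 1.32 kg, about 16% above 1.13. If the target is instead what a new control group would have done, the prediction SE is √(1.5² + 0.67²) = 1.64 kg, close to the top of the range.

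**The case against.** The strongest reply concerns FTC weight. The sentence just before the DID sentence points to the external counterfactuals, and the meta-analysis yields a control change over time. A reader might infer from the absence of enrolled controls that no FTC weight difference can be formed at all. The documents do not support that: it can be formed against the literature. The article also plans to compare the study data with the literature curve at specific time points using the confidence intervals of both, so literature uncertainty does enter that analysis. This stands, and it limits the FTC part to an undefined control and a variance source that omits the control. It does not rescue the DID sentence, which names its own, different variance source.

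A reader might also infer that general members are the intended control, in which case the programme's effect would be partly subtracted from itself. Nothing in the article gives them that role, and the stated model pools them with FTC participants. I do not rely on this reading.

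Finally, the article says openly that there is no control group, and the Abstract describes the Hua Oranga outcome as a change between pre and post scores. That softens the risk of misreading. It does not make the stated reason for DID correct.

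**Conclusion.** The point holds in this form: neither difference-in-difference can be estimated from the models as stated, because they contain programme participants only and no group or control term.

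- **Hua Oranga:** the sentence is wrong as written. Pre and post data on one group give one difference, and no external source is named for a second.
- **FTC weight:** an external, non-concurrent difference is feasible, but not with the control undefined and not from the study's covariance matrix alone.

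The size of the SE understatement is illustrative. It rests on an assumed change SD, an assumed literature SE and independence of the two sources. It would be tempting to say that the FTC interval should be nearly twice as wide. That is the result for SD 8 kg with a literature SE of 1.7 kg (2.04/1.13 = 1.8). The ratio falls to about 1.1 at a literature SE of 0.5 kg, and can exceed 2 with SD 5 kg. The documents do not settle where in this range the study lies. The pooled weight model and the time-point comparison with the literature do not depend on the DID step.

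**What to change.** **Hua Oranga.** Delete the DID sentence. Report the within-person change for each domain and the total with a 95% CI, labelled as uncontrolled.

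**FTC weight.** Replace the DID sentence with wording along these lines: the FTC change from baseline at a stated month, minus the literature-control change predicted for the same month, with variance equal to the variance of the FTC change from the mixed model plus the variance of the literature-control prediction. State whether that second variance is for the mean control curve or for a new control group, since Step 6 shows that this matters. Label the result an external, non-concurrent comparison, and align it with the literature comparison already planned so that there is one such analysis with one variance rule. Because the pooled model has only time as a fixed effect, an FTC-specific change also needs a cohort-by-time term or a separate FTC fit.

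**Cost.** Wording and one variance term, with no new data. The FTC intervals will be wider, and the Hua Oranga result can be claimed only as a change over time.

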### Analysis of hua oranga scores

The hua oranga scores will be analysed with a general or generalised linear mixed model with proper distribution (gaussian, binomial or poisson) depending on the characteristics of the distribution of the outcomes. The random term is the person (participant). The scores per domain will be analysed as well as the sum of all the scores. Because we have pre- and post-data, all analyses will be followed with a DID analysis to obtain the corrected differences.

### Data management

All data will be stored securely on a password-protected shared drive on a University of Auckland with access restricted to the relevant researchers conducting the data collection and analysis.

### Data monitoring

As this is not an intervention study but observation of an existing programme, there is no need for a data monitoring committee nor strategies to stop a trial. Participants can freely chose when they wish to engage with BBM and repeated measurements of their weight and quality of life at the beginning and end of the study has low risk of harm.

### Dissemination

The findings will be published in appropriate peer-reviewed publications, as well as disseminated through community fono and hui (meetings) and conferences. BBM will further disseminate the findings via their social network platforms to BBM members and followers. All researchers who meet the criteria will be authors and no professional writers will be used.

## Discussion

It is important to note that the fundamental question for both our study groups is whether weight loss can be maintained over the long haul. Multiple studies have shown that many diet and physical activity programmes can create short-term weight loss. Similarly, many studies have shown that the loss and maintenance of weight can have important health benefits. The critical remaining questions are implementation-related: How many people can be attracted to a programme (especially from communities with high obesity prevalence), how many can stay with the programme (duration of engagement is closely related to weight loss maintenance), and what are the long-term weight loss results?

If this study demonstrates robust empirical evidence of programme success, this could shift the paradigm for achieving the ultimate public health objective of sustained weight loss in an era of high sedentariness and energy-dense food environment. This paradigm switch, especially for communities with a collectivist culture, may result in a move from the one-on-one advice of expert professionals in a clinic environment, to a many-on-many participation with non-experts in community settings. Internationally, it is the collectivist cultures of indigenous and migrant and minority populations, living within dominant individualist western ideologies, which have much greater burdens of obesity [37]. If a robust and culturally informed evaluation of BBM demonstrates the effective features of this community-based approach to sustained weight loss, this could be of high relevance and benefit to other indigenous and migrant populations. In Aotearoa, achieving equity for Pacific and Māori engagement in health enhancing programmes remains an important strategy for achieving better health and wellbeing outcomes, and quality of life for whānau (family).

Obesity is the consequence of complex, adaptive, societal systems and therefore approaches to deal with obesity (treatment or prevention) need to use systems tools to manage that complexity [8]. There is a lack of evidence implementing systems-level thinking and analyses to evaluate and assist in the evolution of a community programme delivering health and wellbeing services for Pacific and Māori people which uses culturally appropriate methods of inquiry [38]. The partnership of BBM and University of Auckland researchers are exploring the evidence base for BBM using kaupapa Māori and co-design [39], with the aim of improving health outcomes and reducing health inequities [40, 41]. The Pacific approaches of fa’afaletui [42, 43] and fonofale [44], and the similar te whare tapa whā model [45] use an empowerment rather than a deficit model, with a holistic view of physical, mental, spiritual and family / community health in the context of people’s lives.

Our participants are willing partakers of the BBM programme, who have joined to make a change in their health status and lives going forward. Their motivation to engage in research that aims to improve health and wellbeing has been demonstrated in our prior qualitative investigation. Combining indigenous cultural frameworks in the delivery of health support services may prove critical for sustained engagement, and significantly improved outcomes for Pacific and Māori populations.

While a pragmatic before-after study design has no control group, there is very strong evidence that a non-intervention counterfactual of no weight change is plausible, since the average natural trajectory of people with obesity is no change or slow increases in weight. A sustained weight loss of 5–10% is clinically meaningful for health benefits, even if people remain overweight or even obese [2].

Inevitably, the COVID-19 pandemic adds additional challenges. Recurrent Alert Level 4 and 3 lockdowns, the latest in August to October 2021, has delayed initial recruitment. It may be several months before the city is again at Alert Level 1 and full social gatherings can be resumed, including BBM bootcamps. In the interim, BBM provides online classes via their social media platform, as well as distributing hundreds of parcels of donated healthy food daily to vulnerable and socioeconomically disadvantaged members experiencing food insecurity through the financial stresses imposed by the lockdown.

## Data Availability

Not applicable.

## Abbreviations

BBM: Brown Buttabean Motivation
BMI: Body mass index
FTC: From The Couch
GP: General practitioner
PHO: Primary Health Organisation
PIS: Participant Information Sheet
